### Oversight and Monitoring

#### Safety Management

All participants will receive standard antenatal care at every visit by obstetricians. In addition to physical examination, obstetric examination will be performed, including evaluation of fetal growth and fetal heart rate activity, either by clinical or ultrasonographic examinations. Additional procedures will be provided as appropriate, such as electronic fetal monitoring, detailed ultrasonographic examination, etc.

Glycemic control will be evaluated by FPG and 2-hour PPG or percentage of abnormal SMBG test results. Individual nutritional and behavioral counseling will be provided, customized for each participant. According to institutional guidelines, participants with FPG ≥200 mg/dL or glycated hemoglobin ≥10% will be admitted for further evaluation and initiation of insulin therapy by an endocrinologist.

#### Adverse Event Reporting and Harms

Any adverse events will be evaluated by self-report from the participants and by interview and clinical evaluation during each visit (every 2 weeks), starting from the day of enrollment until the end of the study (at 6 weeks after enrollment). In addition, participants will be contacted every 2 days via a telephone call, SMS, or other online platform to evaluate any adverse events. A telephone number will be given to all participants to call if there are any suspected abnormalities or any adverse events. Attending obstetricians will assess whether the events are related to the investigational drugs used for GDM. Management will be provided as appropriate by attending obstetricians, and consultation with other specialists will be made as necessary. In case of any adverse events, an additional specific follow-up schedule with related specialists will be offered until they are resolved or considered stable. Assessment of the adverse events and their response to treatment will be by telephone call, self-report, and clinical and laboratory assessment, as appropriate, according to the contexts and nature of the events. All the events will be followed up on until the conditions resolve. All the adverse events will be recorded in detail in the case record form.

In case of withdrawal or termination of the study protocol, such as severe adverse events or noncompliance, treatment will be unblinded. Further individualized management will be provided as appropriate.

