### Interventions

After initial screening and acquiring informed consent, the women will be randomly assigned to 2 groups—the intervention group or the control group.

For the intervention group, metformin PR will be provided to the participants, starting with 750 mg daily (1 tablet of metformin PR 750 mg). Follow-up is scheduled every 2 weeks for 6 weeks. Dosage adjustment will be made at each visit, depending on the results of glycemic control in a step-up protocol, that is, 750, 1000, 1500, and 2000 mg. The maximum dosage of metformin PR is 2000 mg per day. For dosage adjustment, 1 tablet of metformin PR 1000 mg will be used for a dosage of 1000 mg per day, 2 tablets of metformin PR 750 mg will be used for a dosage of 1500 mg per day, and 2 tablets of metformin PR 1000 mg will be used for a dosage of 2000 mg per day.

Pregnant women who are in the control group will receive 1 tablet of a placebo and will be scheduled for follow-up every 2 weeks for 6 weeks.

In addition to standard antenatal care according to institutional guidelines, pregnant women in both groups will receive individualized counseling on nutrition and behavioral modifications for glycemic control at every follow-up visit.

All participants are encouraged to adhere to the medication provided. A specific phone number will be provided to participants to receive an answer if they have any questions about the medications. Participants will be contacted every 2 days via a telephone call, SMS, or other online platforms to ensure medication adherence. Pill count will be performed at every visit, and additional encouragement will be provided. All participants are advised to avoid using other antidiabetic medications and other herbal products during the study period.

At the end of the study period of 6 weeks, glycemic control will be evaluated thoroughly, and appropriate treatment will be provided. Either the previous treatment will be continued or a new treatment will be initiated, after consultation with an endocrinologist, as appropriate. Standard antenatal care will also be provided until delivery. Treatment failure is defined as inadequate glycemic control after 2000 mg of metformin PR. In such a situation, insulin therapy is initiated.

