If any of the conditions in the exclusion criteria are detected after enrollment, such as congenital anomalies, randomization concealment will be revealed and considered as a dropout, and these participants will not be included in the analysis. The pregnant woman will be thoroughly evaluated by the obstetrician team to provide appropriate management.

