### Outcomes

The primary outcome of this study is the rate of achievement of optimal glycemic control within 6 weeks, which is defined as FPG <95 mg/dL or 2-hour PPG <120 mg/dL in >80% of total SMBG test results.

The secondary outcomes include time to achievement of optimal glycemic control, rate of insulin therapy, and rate of side effects. Treatment failure is defined as inadequate glycemic control after 2000 mg of metformin PR. In this situation, insulin therapy is initiated. Side effects will be evaluated by interviewing the participants at each visit and by additional contact via a telephone call, SMS, or other online platforms.

The participant timeline is displayed in Figure 1.

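### Collection of new adverse events stops at 6 weeks although treatment may continue, so later fetal and neonatal events are missed; a separate rule drops some earlier fetal events from the analysis

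*Protocol article*

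**What the plan says.** All references are to the protocol article.

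- **Adverse Event Reporting and Harms** sets the collection period as "starting from the day of enrollment until the end of the study (at 6 weeks after enrollment"). For events already found it adds: "All the events will be followed up on until the conditions resolve".
- **Interventions** covers the time after week 6: "Either the previous treatment will be continued or a new treatment will be initiated, after consultation with an endocrinologist, as appropriate". No end date is given for a continued treatment. The sentence that reaches delivery concerns care, not study drug or data: "Standard antenatal care will also be provided until delivery".
- **Safety Management** describes what is done at visits: "obstetric examination will be performed, including evaluation of fetal growth and fetal heart rate activity, either by clinical or ultrasonographic examinations".
- **Outcomes** lists the secondary outcomes: "The secondary outcomes include time to achievement of optimal glycemic control, rate of insulin therapy, and rate of side effects". No fetal, delivery or neonatal item appears there or among the data named in Data Collection and Management.
- **Eligibility Criteria** excludes fetal anomalies or death and suspected fetal growth restriction. For growth restriction it gives the reason that metformin calls for caution there.
- **Interventions** also states what happens if an exclusion condition is detected after enrollment: "randomization concealment will be revealed and considered as a dropout, and these participants will not be included in the analysis". **Statistical Methods** puts every analysis on an intention-to-treat basis.
- **Strengths and Limitations** notes that 6 weeks may miss long-term effects and that the study is not designed to show better pregnancy outcomes. It does not mention late harm.

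**The concern.** This is a placebo-controlled drug trial in pregnancy. Its window for new adverse events closes while the woman is, in most cases, still pregnant, and treatment begun in the trial may run past that point. An event that first appears in week 7 or at birth is therefore not collected in either arm. Following known events to resolution does not help, because it applies only to events found before the window closes.

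The rule on exclusion conditions adds a second loss, this time inside the window. Growth restriction and fetal death are exclusion conditions. Read literally, a woman who develops one after randomization is unblinded, counted as a dropout and left out of the analysis. Those are the women a safety comparison most needs to keep.

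At stake is what the report can say about safety. The Dissemination section says the findings could help modify current guidelines. The Conclusions say that, if effective, the drug could be considered a good alternative to the immediate-release form or insulin. A safety statement that ends at 6 weeks and omits women with certain fetal events is thin support for either.

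**Working it through.** The plan gives no figure for safety coverage, so there is none to reproduce on this point. The size of the gap is worked out from the plan's timings plus stated assumptions.

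**1. How long after the window closes does pregnancy continue?**

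Inputs from the documents: screening at the first antenatal visit and again at 24 to 28 weeks (GDM Diagnosis and Management); up to 4 weeks of repeat counseling before drug treatment under institutional practice (same section); a 6-week window (Adverse Event Reporting and Harms).

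Assumptions: a first-visit diagnosis at 12 weeks, the full 4 weeks between diagnosis and randomization (not an inclusion condition), and delivery at 37 to 40 weeks.

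Closure = diagnosis week + 4 + 6. Uncovered time = delivery week − closure, with a minimum of 0.

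| Diagnosis (weeks) | Window closes (weeks) | Uncovered, delivery at 37 | Uncovered, delivery at 40 |
|---|---|---|---|
| 12 | 12 + 4 + 6 = 22 | 15 | 18 |
| 24 | 24 + 4 + 6 = 34 | 3 | 6 |
| 28 | 28 + 4 + 6 = 38 | 0 | 2 |

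Whenever delivery falls after closure, the birth outcome is missed, however short the gap.

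**2. How many metformin women could continue treatment?**

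The sample-size paragraph gives 40 per group, a 20% loss and 95% success within 6 weeks on metformin.

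- Retained: 40 × (1 − 0.20) = 32.
- Expected to reach target: 0.95 × 32 = 30.4, about 30.

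These women could continue treatment. The documents do not say how many will.

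**3. What could birth data from a trial of this size show?**

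With no events among n women, the one-sided 95% upper limit for the event rate is 1 − 0.05^(1/n).

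- n = 40: 7.2%.
- n = 32: 8.9%.

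The data would describe, not test.

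**4. The rules side by side**

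| Fetal event | Recorded? | Analysed? |
|---|---|---|
| Within 6 weeks, not an exclusion condition | Yes | Yes |
| Within 6 weeks, an exclusion condition (growth restriction, fetal death, anomaly) | Yes, as an adverse event | No under the dropout rule; yes under intention-to-treat |
| First arising after week 6, or at birth | No | No |

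The second row is a contradiction within the document. The third follows from the stated collection window.

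**The case against.** The strongest reply is that the 6-week boundary is deliberate and consistent. Study Design, Interventions, Outcomes and the limitations all use it. The limitations partly disclose it, since long-term effects could be read to include harm. The article also condenses a fuller protocol: its data list gives examples only, and the board's charter is not shown. Later management is individualized, so differences at birth would be hard to attribute to the randomized drug, and the numbers are small.

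Much of this stands. It limits what the birth data can prove and rules out several stronger readings:

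- **That fetal harm lies wholly outside the safety data.** It does not. Fetal growth and heart rate are examined at visits, all adverse events are recorded, and known events are followed past week 6.
- **That study drug continues until delivery.** Only antenatal care is said to do so. Treatment may continue, with no end stated. Metformin is already in the institutional guideline, so later use may be routine care.
- **That growth restriction is a late drug effect, or the only fetal risk named.** The exclusion criteria give a caution about use where it exists, with no time course, and they also list anomalies and deaths.
- **That 38 of 40 metformin women would be at target at week 6.** This ignores the 20% loss, and the plan's rate is for success within 6 weeks, not at week 6.
- **That the board will see no birth outcomes.** The article does not say what it reviews.
- **That the two descriptions of when event follow-up ends are a contradiction.** One concerns the specialist follow-up offered and the other follow-up of events. This is loose wording.

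The reply does not remove the main point. The 6-week end of collection is an explicit rule, not a detail left to another document, and the limitations tie the study's end to pregnancy benefit without mentioning safety. Small numbers argue for descriptive reporting, not for leaving the data uncollected.

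**Conclusion.** The concern holds in limited form. New fetal and neonatal events after week 6, including birth outcome, are not collected although the previous treatment may continue, and this is not acknowledged as a safety limitation. Separately, the rule that removes women with an exclusion condition found after enrollment conflicts with intention-to-treat and, read literally, takes women with growth restriction or fetal death out of the analysis.

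The size of the gap depends on gestational age at enrollment, which is not given. Under the assumptions above it runs from 15 to 18 weeks for diagnosis at 12 weeks down to 0 to 2 weeks for diagnosis at 28 weeks. About 30 of 32 retained metformin women could be treated beyond the window. The primary efficacy question at 6 weeks is not affected by the collection window, but the dropout rule does affect who is analysed for it. This is a worthwhile and inexpensive improvement, not a flaw that invalidates the trial.

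**What to change.** 1. Keep the 6-week efficacy period. In Adverse Event Reporting and Harms, extend safety data collection to delivery for every randomized woman in both arms.
2. Abstract from routine records: gestational age at delivery, birth weight and size for gestational age, stillbirth or neonatal death, neonatal hypoglycemia and admission, preeclampsia, and any glucose-lowering drug used after week 6.
3. Report these descriptively by randomized arm and send them to the data safety monitoring board.
4. Reconcile Eligibility Criteria, the dropout rule in Interventions, Statistical Methods and Adverse Event Reporting and Harms, so that women with fetal events found after enrollment stay in the safety and intention-to-treat analyses. This concerns who is analysed; no treatment rule is proposed.
5. If collection cannot be extended, state in the limitations that safety is known only to week 6.

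**Cost.** One amendment and one record-based form, with no added visits or procedures. The final safety report would come some months after the planned October 2026 completion: up to about 18 weeks for the last woman enrolled under the earliest diagnosis assumed here. Publication is planned for 2027. A few deliveries at other hospitals would need a call, and women already enrolled may need renewed consent. With 40 per arm, the data remain descriptive only.

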#### Data Safety Monitoring Board

An independent data safety monitoring board will be set up for trial monitoring. The members will include 2 obstetricians, 1 endocrinologist, 1 biostatistician, and 1 methodology expert. None of the data safety monitoring board members has any conflicts of interest that may affect the decision-making process.

### Ethical Considerations

At the antenatal care clinic, the investigator or the research assistant will screen pregnant women with GDM for eligibility and provide detailed information regarding the study. If the women agree to participate, a written informed consent will be obtained. Each participant will receive compensation of US $30. The study has been approved by the Siriraj Institutional Review Board (Si106/2025). All personal identification information of the participants, including names, telephone numbers, hospital numbers, and medical records, will be anonymized to ensure confidentiality. Coding will be used for each participant, and no related information will be disclosed. All study data will be stored by the researchers and will be retained for at least 5 years after publication.

### Dissemination

The research findings will be disseminated to relevant stakeholders, including participants, their families, physicians, and the institutional medical community. In addition, the results will be disseminated via high-impact international peer-reviewed medical journals and presentations at international medical conferences to ensure broad academic and clinical engagement. Reporting the results of the study will follow the latest CONSORT (Consolidated Standards of Reporting Trials) guidelines. Distribution of key information will also be made available for health care professionals and the public, as appropriate.

The findings will also be disseminated at the national level via various medical institutions, obstetrics and gynecology communities, endocrinology communities, and the Ministry of Public Health. These findings could help modify the current guidelines for GDM management.

## Results

The study was funded in May 2025, when recruitment started. Women with GDM who had inadequate glycemic control by nutritional therapy were assessed for eligibility. As of June 2025, 24 women with GDM agreed to participate and follow-ups were scheduled. Recruitment will continue until 80 participants are included, which is expected to occur by September 2026. The study is projected to be completed in October 2026. The results are expected to be published in 2027.

## Discussion

### Anticipated Findings and Importance

Although the effectiveness of metformin in the treatment of GDM has been demonstrated in previous studies, only metformin IR has been investigated [4-14]. No study has specifically reported the effectiveness of metformin PR, which could have advantages over metformin IR in terms of fewer side effects and a once-daily dosage that results in better compliance [23-28]. Moreover, no previous study has reported the time required to achieve glycemic control after metformin treatment.

Therefore, the results of this study will add additional information to the medical community. It can help caring physicians to make better decisions regarding the selection of appropriate dosage and formulation of metformin, as well as a follow-up schedule for evaluation of glycemic control. In addition, the results could also help identify women at a higher risk for unsuccessful glycemic control after metformin therapy.

Some challenges in conducting the study might include adherence to the scheduled treatment and follow-up. Various measures are planned to improve both important issues. All participants will be informed regarding the importance of adherence to the treatment and follow-up to achieve glycemic control. Participants will be regularly contacted every 2 days via a telephone call, SMS, or other online platforms to encourage adherence to the provided medications and follow-up schedule, and for the evaluation of any adverse events.

The results will provide more insights into the use of metformin PR for the treatment of GDM. Understanding its effectiveness, time to achieve glycemic control, as well as the risk for treatment failure, can help caring physicians make better decisions on treatment initiation and follow-up schedule for glycemic control evaluation, and identify those who are at higher risk for treatment failure. All the information would be helpful in developing a higher quality of care for patients with GDM in the future.

### Strengths and Limitations

The strengths of this study include its randomized, double-blind, placebo-controlled trial design. The diagnosis of GDM follows a uniform institutional guideline. Nutritional and behavioral modifications counseling is provided by well-trained, certified diabetes educator nurses. The main outcome of glycemic control is objectively measured.

Some limitations include that the duration of the intervention and follow-up to evaluate the primary outcome of glycemic control within 6 weeks might not fully capture the long-term effects or improvements after metformin PR treatment. A longer follow-up period is needed to determine whether a higher dose of metformin PR or insulin will be required to achieve adequate glycemic control as pregnancy progresses. In addition, the actual dietary and behavioral practice varies among participants and cannot be accurately measured, which could affect the outcomes. Moreover, the study does not provide a head-to-head comparison between different formulations of metformin, that is, IR versus PR.

The study is not primarily designed to determine if the use of metformin PR improves the pregnancy outcomes, as the study ends at 6 weeks after initiation of the treatment, and further management will vary according to the status of the women and physicians’ discretion. Further well-designed studies on the improvement of GDM-related maternal and neonatal outcomes, such as preeclampsia, large-for-gestational-age infants, and macrosomia, with metformin therapy should be conducted to provide additional evidence on metformin benefits and help aid clinicians’ decisions.

The study is planned to be a pilot randomized clinical trial, and the sample size was calculated based only on the primary objective of comparing glycemic control between the 2 groups and did not take into account for some related factors, such as BMI or gestational age. However, this issue should be considered when designing larger definitive studies in the future. Acknowledging these limitations is essential for interpreting the results and refining future research.

### Conclusions

This study is primarily aimed at investigating whether metformin PR is effective in the treatment of GDM in terms of achievement of glycemic control within 6 weeks and time to achieve glycemic control. This information will provide additional evidence on the potential benefits of metformin treatment in GDM that can be applied to clinical practice. If metformin PR is effective in achieving glycemic control within a short time, it can be considered a good alternative to conventional IR formulation or insulin. In addition, the results will serve as a basis for future research to explore the benefits of treatment, especially if the treatment can improve maternal and neonatal outcomes.

## Data Availability

The datasets generated or analyzed during this study are available from the corresponding author on reasonable request.

## Abbreviations

FPG: fasting plasma glucose
GDM: gestational diabetes mellitus
IR: immediate-release
PR: prolonged-release
SMBG: self-monitoring blood glucose
